## 9.2. ***Lost to Follow-up***

A participant will be considered lost to follow-up if he/she is unable to be contacted by the study site.

The following actions must be taken if a participant fails to comply with required study procedures:

- The site must attempt to contact the participant as soon as possible and counsel the participant on the importance of maintaining the assigned procedure schedule and ascertain whether or not the participant wishes to and/or should continue in the study.
- Before a participant is deemed lost to follow-up, the Investigator or designee must make every effort to regain contact with the participant (where possible, 3 telephone calls and, if necessary, a certified letter to the participant's last known mailing address or local equivalent methods). These contact attempts should be documented in the participant's medical record.
- Should the participant continue to be unreachable, he/she will be considered to have withdrawn from the study with a primary reason of lost to follow-up.

## **10. Study Encounters**

### **10.1. For Brazil**

The current COVID-19 pandemic has placed a significant burden on the healthcare system. For this study, specimen and data collection will be conducted to minimize impact of non-ill participants within the healthcare system. If the participant is assessed as eligible, contact between study participants and study personnel will occur in person should the participants are identified at primary care setting, via a telephone, or through home visits by local physician assistants and medical students with PPE.

Participants will be instructed to seek clinical care should they manifest any signs or symptoms of LRTI requiring medical intervention.

#### **10.1.1. Screening/Baseline Evaluation: Day minus 1/0**

Participants will be assessed for study eligibility through a screening conducted through a home visit. Screening/Day minus 1 and Day 0 procedures can occur on the same day.

#### **Day minus 1 evaluations are as follows:**

- Informed consent
- Eligibility criteria review
- Collection of demographic information
- Use of tobacco and alcohol
- Illegal substance abuse
- Collection of past and current medical conditions, including known pregnancy and/or lactation status
- Urine pregnancy test for women with at least one menstruation in the last 12 months
- Nasopharyngeal or saliva sample collection for RT-PCR for SARS-CoV-2 confirmation
- Collection of information regarding exposure to the index case
- Assessment of respiratory signs and symptoms

#### **The participant will do the following on Day 0:**

- Interactive Web Response System (IWRS) registration and randomization after PCR confirmation (the expected turn around for PCR testing is 12-24 hours)
- Recheck the inclusion / exclusion criteria and verify the participant's interest in continuing in the study
- Physical examination, including weight, height, vital signs measurement (seated/supine PA, pulse rate, and temperature)
- Collection of concomitant medication information
- Delivery of medications and guidelines for the assigned medications
- Delivery of medicines under investigation. The patient will receive the drugs under investigation as allocated by IWRS (patients in the placebo group will receive the standard treatment defined by the assistant team) and the necessary instructions for use.

- Patient will receive a card with 24-hour telephone contact to call if necessary. Patient will be guided on daily telephone contact and on the collection kits for viral load research.
- Take study therapy (as assigned)
- Tolerance towards the assigned therapy
- Confirmation of adherence to study therapy dosing
- Daily dosing time
- Reporting of adverse events
- Cardiac measurement using Kardiamobile monitors
- SpO2, respiratory rate, temperature and pulse measurements
- Measurement of heart rate (pulse oximeter) at rest after the participant remained seated at rest for 5 minutes
- Blood pressure measurement after the participant was seated at rest for 5 minutes
- Clinical symptoms review
- WURSS-11 survey for dyspnea
- Tisdale scale
- EQ-5D-5L
- Guidance on daily telephone contacts
- COVID-19 guidelines and quarantine recommendations

Eligible participants will be randomized. Participants will be instructed how to self-assess respiratory rate. Local health care providers wearing personal protective equipment will deliver and collect study related mid-nasal swabs and DBS cards as needed.

Participants will be assessed at the home visits during the mid-nasal swab or saliva collection thermometer, Kardiamobile device, and pulse oximetry device.

The SARS-CoV-2 positive test results will be confirmed through laboratory records.

Patients tested negative for COVID-19 will be considered a screening failure, and only positive patients will be treated and invited for subsequent follow-ups.

#### **10.1.2. Day 1 Through Day 14**

The participant will do the following every day from Day 2 through Day 14 (unless stated otherwise), inclusive:

- Take study therapy (for a total treatment of 10 days of treatment)
- Tolerance towards the assigned therapy
- Confirmation of adherence to study therapy dosing (Day 10)
- Daily dosing time from the day prior
- Reporting of adverse events
- Cardiac measurement using Kardiamobile monitors (Day 3, Day 7, Day 10, and Day 14)
- Pulseoximeter measurements (Day 3, Day 7, Day 10, and Day 14)

| Harmonized protocol document                                                          |
|---------------------------------------------------------------------------------------|
| Short title: Outpatient Management of SARS-CoV-2 for High-Risk Adults in LMICs |

- Measurement of heart rate (pulse oximeter) at rest after the participant remained seated at rest for 5 minutes
- Review of clinical symptoms and hospitalization
- WURSS-11 survey for dyspnea

A study team member will be available via Telehealth, text messaging, or telephone to provide support for completion of study procedures. Participants will be clinically assessed for signs and symptoms of respiratory distress and will have in person assessment of AEs. As needed, additional contact with the study clinician or staff will be conducted at the request of the participant (e.g., if developing concerning symptoms or an adverse event) or if needed to clarify study procedures or follow-up symptoms.

The health care provider will make home-visits to collect nasal-swabs or saliva samples for RT-PCR on Day 3, Day 7, Day 10, and Day 14. These samples collected on Day 14 will be used to analyse the viral shedding related outcomes. Other samples collected on Day 3, Day 7 and Day 10 will be stored for a biobanking deposit.

A study team member will be available via Telehealth, text messaging, or telephone to provide support for completion of study procedures.

Clinical outcomes will be confirmed through the electronic health record, if possible.

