## Rationale:

Despite the fact that most hospitals are already overwhelmed and hospitalization will not be feasible even for severe COVID-19 cases in most of low- and middle-income countries (LMICs), the majority of current clinical trials is taking place in hospital settings and in high-income countries (HICs) ([www.covid19-trials.org](http://www.covid19-trials.org)). Many of these trials are also excluding marginalized population groups such as people living with HIV (PLHIV) and people with active or latent tuberculosis (TB) who are key populations of interest for LMICs. The burden of HIV and TB in LMICs is generally much higher than in HICs.

There is a need to immediately start the clinical investigation of outpatient strategies in these resource-limited regions that are inclusive of these marginalized groups.

This protocol is for an adaptive platform trial for the treatment of high-risk adults with severe acute respiratory syndrome coronavirus 2 (SARS-CoV-2) infection not requiring hospital admission for Brazil, hereafter referred to as TOGETHER 2. This proposal builds on an US-based adaptive platform trial for high-risk SARS-CoV-2 adult outpatients (hereafter referred to as TOGETHER 1).

The primary research question is to the efficacy of experimental interventions to prevent LRTI among persons with SARS-CoV2 infection who are at high risk of progression. The primary outcomes of trial will include progression to LRTI, defined by SpO2<93% or 6% decrease in SpO2 from baseline; and presence of viral shedding from nasal swabs at day 10 of treatment. Other agents are rapidly being screened and developed for SARS-CoV-2 infection and could be incorporated into this protocol as additional arms. The flexible platform trial design will allow additional agents to be added and tested with standardized eligibility criteria, outcomes, and measurements. If an intervention is shown to be effective, this design would allow replacement of the placebo group with the effective intervention as the comparator.

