| Pregnancy Test                                                                               | X                                  |                                                     |                               |                              |                               |                              |                               |                               |                               |                               |                                                        |
| Mid-nasal swab or saliva for SARS-CoV-2 confirmation and viral load assessment (D0, and D14) | X                                                |                                                     |                               |                              |                               |                              |                               | X                             |                               |                               |                                                        |
| Mid-nasal swab or saliva for biobanking deposit (D3, D7 and D10)                             |                                                  |                                                     |                               | X (D3)                       | X (D7)                        |                              | X                             |                               |                               |                               |                                                        |
| Concomitant medications                                                                      | X                                                |                                                     |                               | X (D3)                       | X (D7)                        |                              | X                             |                               |                               |                               |                                                        |

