| 
 
To test whether any of the experimental interventions is associated with decreased viral shedding from self-collected nasal swabs over 14 days: Day 1, Day 10 and Day 14 (+/-1 days)
 
 | 
 
Proportion of days with SARS-CoV-2 detected from mid-nasal swabs by PCR
 
Change in viral load on day 10 and day 14 after randomization from baseline
 
                                                                                                                                                                                                                                                                                                                                                                                                                                                                                                                                             |
| 
 
To test the quality-of-life (QoL) of experimental interventions for treatment of high-risk outpatients with SARS-CoV-2 infection
 
                                                     | 
 
Change in quality of life measured by Eq-5D-5L from baseline
 
                                                                                                                                                                                                                                                                                                                                                                                                                                                                                                                                                                                                                                             |

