### **11.1. Efficacy Assessments for Brazil**

#### **11.1.1. Mid-nasal swab or saliva for Brazil**

Health care providers will collect mid-nasal swabs or saliva samples from participants for viral detection at Day 1, Day 3, Day 7, Day 10 and Day 14 (+/-1 day).

Swabs or saliva will be subjected to RNA amplification and tested for SARS-CoV-2 by the local laboratory or by a laboratory designated by it.

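### The protocol contradicts itself on whether the Day 3, 7 and 10 viral samples are assayed; if the Schedule of Activities governs, the listed Day 10 viral endpoints have no data

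*Protocol*

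**What the plan says.** **Endpoints.** The viral-shedding objective in 4.1 concerns "decreased viral shedding from self-collected nasal swabs over 14 days: Day 1, Day 10 and Day 14 (+/-1 days". Its endpoints include "Proportion of days with SARS-CoV-2 detected from mid-nasal swabs by PCR" and "Change in viral load on day 10 and day 14 after randomization from baseline". The Synopsis table carries the same two endpoints. The Synopsis rationale also counts "presence of viral shedding from nasal swabs at day 10 of treatment" among the trial's primary outcomes. Both tables list clearance as a secondary endpoint, met by a single negative swab, with no day named.

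**Text that limits the assays.** Section 2.1 has two separate sample rows: "Mid-nasal swab or saliva for SARS-CoV-2 confirmation and viral load assessment (D0, and D14") and "Mid-nasal swab or saliva for biobanking deposit (D3, D7 and D10"). Section 10.1.2 says that the Day 14 samples serve the viral shedding outcomes, and then: "Other samples collected on Day 3, Day 7 and Day 10 will be stored for a biobanking deposit".

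**Text that assays the other days too.** The same paragraph of 10.1.2 opens by saying that the Day 3, 7, 10 and 14 samples are collected for RT-PCR. Section 11.1.1 reads: "Health care providers will collect mid-nasal swabs or saliva samples from participants for viral detection at Day 1, Day 3, Day 7, Day 10"; its list ends with Day 14. Its next paragraph has swabs or saliva amplified and tested, with no day excepted. Sections 8.1.2 and 10.1.7 call for PCR swabs on Days 3, 5, 7 and 10.

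**The concern.** An endpoint measured at Day 10 needs a Day 10 result. Two separate places in the protocol, the Schedule and 10.1.2, send the Day 10 sample to storage and name no later assay. The introductory bullets of sections 9 and 11 (both titled Study Assessments and Procedures) require adherence to the Schedule, so a site or laboratory that follows it would bank the Day 10 sample.

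At stake are the viral secondary endpoints: one time point could be empty, one endpoint could become redundant, and clearance could be counted in two different ways. An analysis plan cannot repair this later, because which specimens are tested is a matter of trial conduct and untested samples give no results to analyse.

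**Working it through.** The protocol states no figure to reproduce. The check compares the assayed days with what each endpoint needs.

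**1. Assayed days under each reading**

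| Source | Assigned to PCR, detection or viral load | Banked |
|---|---|---|
| 2.1 Schedule | D0, D14 | D3, D7, D10 |
| 10.1.2, closing sentences | D14 | D3, D7, D10 |
| 10.1.2, opening sentence of the same paragraph | D3, D7, D10, D14 | none |
| 11.1.1 | D1, D3, D7, D10, D14 | none |
| 8.1.2 and 10.1.7 | D3, D5, D7, D10 | none |
| 4.1, objective | D1, D10, D14 | none |

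The conflict goes beyond Day 10. Day 5 appears only in 8.1.2 and 10.1.7, and the baseline sample is called D0 in one place and Day 1 in others.

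**2. Change in viral load.** Under 2.1, the change from D0 to D14 can be computed and the change from D0 to D10 cannot. Under 11.1.1, both can.

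**3. Proportion of days with virus detected.** Let X_d = 1 if virus is detected on day d, and 0 otherwise.
- Under 2.1, counting post-baseline days only, the proportion is X_14 / 1, which takes the values 0 or 1. This is Day 14 positivity itself.
- Under 2.1, counting baseline as a day, it is (X_0 + X_14) / 2. With a positive baseline this is 1/2 or 1, again a relabelling of Day 14 status.
- Under 11.1.1, counting post-baseline days, it is (X_3 + X_7 + X_10 + X_14) / 4, which takes five values from 0 to 1 and does carry information on duration.

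**4. Clearance.** Consider a hypothetical participant who is negative on Day 10 and positive on Day 14. Under 2.1 this person has not cleared, because Day 14 is the only follow-up assay. Under 11.1.1, if any single negative swab counts, the same person has cleared.

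**5. Reduced swabbing.** Sections 8.1.2 and 10.1.7 allow collection to be cut to Days 5 and 10 where multiple swabbing is not feasible, and 8.1.4 and 10.1.9 allow the Day 14 swab to be omitted. Under 2.1, a participant on both reductions would have no assayed post-baseline sample, although a Day 10 sample exists.

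**6. Number of samples.** At 492 per arm and three arms (12.1 and 5.1), there are at most 492 x 3 = 1,476 Day 10 samples. All three banked days together give at most 1,476 x 3 = 4,428. Both counts assume complete collection.

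**The case against.** The strongest reply is that the protocol does provide for testing. The opening sentence of the 10.1.2 paragraph, section 11.1.1 and sections 8.1.2 and 10.1.7 all assign Day 10 samples to PCR or viral detection, and a banked sample can be thawed and assayed. This stands against the claim that Day 10 endpoints cannot be computed at all, which a reader of 10.1.2 alone might infer. It does not remove the conflict: the Schedule and 10.1.2 separate the viral load samples from the biobank samples, and no text says that the banked ones will be tested for these endpoints.

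Three further inferences are tempting and not supported.

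- *The proportion of days can only be 50% or 100%.* This needs every randomized participant to be positive at baseline and baseline to count as a day. Section 6.1.1 accepts a positive test from the past 72 hours, and the note to 6.1.2 provides for patients who have already started therapy and then test negative at screening. Section 10.1.1 treats negatives as screen failures, so the text is mixed, while the ITT population in 12.2 is everyone randomized. The companion symptom endpoints count days after randomization. What stands is that only one post-baseline sample is assayed.
- *A primary outcome is lost.* The Synopsis rationale does call Day 10 shedding primary, and sections 3 and 3.2.5 call viral shedding co-primary or primary. Both formal objectives tables, however, make hospitalization and mortality primary and list the viral endpoints as secondary. That disagreement is a separate matter.
- *Day 14 would miss an antiviral effect because dosing has ended.* The documents contain nothing that shows this.

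**Conclusion.** The protocol is wrong as written, through an internal inconsistency. It gives incompatible instructions on whether the Day 3, 7 and 10 samples are assayed.

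If the Schedule and the closing sentences of 10.1.2 govern:
- Day 10 change in viral load and Day 10 shedding have no data;
- the proportion-of-days endpoint adds essentially nothing to Day 14 positivity;
- clearance reduces to a negative Day 14 sample.

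If 11.1.1 governs, the Day 10 endpoints can be computed, and the Schedule and 10.1.2 are wrong. Change in viral load at Day 14 can be computed under either reading when both samples are available.

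The damage is confined to endpoints that the formal tables list as secondary; hospitalization and mortality are not affected. The sponsor should correct this before samples are processed. The conclusion rests on the sampling and endpoint text alone and on no assumed rate, effect or sample size.

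**What to change.** Choose one of two routes.

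1. **Assay Day 10.** In 2.1 and 10.1.2, move Day 10 from the biobank to viral load assessment and batch-test the samples already being collected. The cost is up to 1,476 assays at 492 x 3, with no added visit. State which days enter the proportion-of-days endpoint and which day or days define clearance. If Days 3 and 7 remain banked, the proportion rests on Days 10 and 14 only, and the text should say so.
2. **Drop Day 10.** Delete the Day 10 and proportion-of-days endpoints and name Day 14 as the time point for clearance. This costs no assays.

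In either case, make these places agree on collection days, assayed days and the baseline label: the Synopsis (rationale and endpoint table), 2.1, 4.1, 8.1.2 and 10.1.7 (the Day 5 swab and the reduced schedule), 8.1.4 and 10.1.9 (the optional Day 14 swab), 10.1.2 and 11.1.1. If Day 14 becomes the only follow-up assay, the permission to omit that swab must be reconciled with its role as the sole source of the viral endpoints.

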#### **10.1.3. Day 28 (+/- 5 days)**

Participants will be followed-up via Telehealth, text messaging, or telephone:

- EQ-5D-5L
- Review of AEs, clinical symptoms, and hospitalization

#### **10.1.4. Day 56 (+/- 5 days)**

Participants will be followed-up via Telehealth, text messaging, or telephone:

- Review of clinical symptoms, and hospitalization

#### **10.1.5. Day 90 or early termination (+/- 5 days)**

Participants will be followed-up via Telehealth, text messaging, or telephone:

- Review of clinical symptoms, and hospitalization
- EQ-5D-5L

#### **10.1.6. Screening/Baseline Evaluation: Day 0/1**

Screening and enrolment will be done with the participant physically present.

**Day 0 evaluations are as follows:**

- Informed consent
- Collection of demographic information
- Collection of past and current medical conditions, including known pregnancy and/or lactation status
- Collection of concomitant medication information
- Collection of information regarding exposure to the index case

|                                          |                 |
|------------------------------------------|-----------------|
| Date/version: May 19, 2020 – V1.0 | Page: 39 |
|------------------------------------------|-----------------|

| Harmonized protocol document                                                          |
|---------------------------------------------------------------------------------------|
| Short title: Outpatient Management of SARS-CoV-2 for High-Risk Adults in LMICs |

- Check of inclusion and exclusion criteria
- Collect mid-nasal swab for PCR

Eligible participants will be randomized. Participants will receive a monitoring kit at enrolment, which will include thermometer and SpO2 device. Participants will be instructed how to self-assess respiratory rate, temperature and oxygen saturation. A study driver wearing personal protective equipment will deliver and collect study related mid-nasal swabs and DBS cards as needed.

**The participant will do the following on Day 1:**

- Take study therapy (as assigned)
- Complete Daily Survey (online, telephone, or text messaging). This Survey will include confirmation of adherence to study therapy dosing and daily swab collection, concomitant medication review, and symptoms review and objective measures including SpO2, respiratory rate, temperature and pulse. In addition, the Baseline Dyspnea Index survey will be completed.

*Instructions for skin puncture and DBS sample preparation are provided in Appendix 4. A study team member will be available via Telehealth, telephone, or text messaging to provide support for completion of this study procedure.*

